### Participants

The target population of this clinical study includes patients with symptomatic hemorrhoids, who require wound treatment after Milligan-Morgan or Parks hemorrhoidectomy.

All adult patients (age ≥ 18 years) suffering from symptomatic hemorrhoids of grade III or IV and scheduled for hemorrhoidectomy by the Milligan-Morgan or Parks procedure are eligible for the NoTamp study. Study participants must be fully legally competent and need to provide written informed consent before randomization, inclusion in the trial, and any trial-related procedure.

Patients with inflammatory anal diseases such as abscesses, fistulas, or gangrene, and pregnant women (according to the patient’s self-report) will be excluded from participation in this clinical study. Patients who are in a dependency and/or employment relationship with the study leader or any of the study staff are not allowed to be included in the trial.

Any inability of the patient to respond to requests, to adequately assess risk, or to comply with the requirements of the course of study, both in the inpatient and outpatient therapy episode, must be considered as non-compliance. If, in the estimation of the clinical investigator, a patient is non-compliant at the time of inclusion or is expected to be non-compliant during the course of the trial, this patient may not be included. Patients participating in other clinical trials that are expected to affect the outcome of the NoTamp-study will not be included.

Figure 1 provides a full overview of the inclusion and exclusion criteria. Reasons for non-enrolment or non-eligibility will be documented for all patients who fulfil the inclusion criteria but who are not included in the trial.

**Fig. 1 Fig1:**
[figure not shown]
Inclusion and exclusion criteria

### Intervention and comparison

In the intervention group, no tamponade dressing will be placed in the rectum of the patient after achieving complete hemostasis. The rectum and anus will be cleaned and a pad with high-absorbence capacity will be placed on the aperture to absorb potential blood loss. The pad will be fixed with mesh pants.

In the control group a tamponade dressing is to be placed in the patient’s anal canal and lower rectum after complete hemostasis. The intraoperatively inserted tamponade remains in the rectum of the patient at least until first defecation and possible spontaneous removal, but usually for a maximum of 24 h. Tamponade dressings may be used according to clinical routine. The type of tamponade used for the study participants will be recorded in the case report forms (CRF).

### Previous and concomitant medication and therapy

The NoTamp study focuses on the evaluation of post-surgical wound treatment. The surgical procedure takes place followed by postoperative care. The surgical procedures allowed in this study include Milligan Morgan’s open hemorrhoidectomy and Park’s submucosal hemorrhoidectomy. Both surgical procedures remove the excessive hemorrhoidal tissue and result in an open wound that needs further treatment.

Thrombosis prophylaxis with low-molecular-weight heparin is mandatory for all patients. Rectal cleansing (preoperative), urinary catheters, analgesics, stool control, and topical applications (ointments) are optional. Discharge management and postoperative controls are usually customized to the individual patient. Pain therapy and prophylaxis include local anesthetics, opioids, non-steroidal anti-inflammatory drugs, muscle relaxants, and other medications such as diosmin and/or sucralfate. During the postoperative period in the recovery room, the patient may receive intravenous or oral pain medication as needed. Subsequently, patients in both treatment groups may receive analgesics as needed until a correspondingly low level of pain (numeric rating scale (NRS) ≤ 3) or freedom from pain is achieved.

After hospital discharge, patients are asked to record their pain medication with type, frequency and amount of intake and to provide this information for documentation in the CRF at the study visit after 7 days. An appropriate supporting documentation template will be provided for the patient.

All previous and concomitant medication will be administered as per clinical routine and according to the patient’s needs and demands. All drugs and other treatments administered will be recorded in the CRF. Since this study represents an evaluation of clinical routine, no treatment guidelines are given.

### Primary and secondary outcomes

Primary outcomes of the NoTamp study are maximum postoperative pain, as measured by a numerical rating scale (NRS) at four time points within 48 h after the surgical procedure, and the occurrence of postoperative bleeding with the need for surgical revision within 7 days after hemorrhoidectomy. Postoperative pain is measured at rest within routine care at 6, 12, 24, and 48 h after the surgical procedure. The most severe pain within 48 h of the surgical procedure will be compared between the treatment groups.

As a secondary outcome, the postoperative pain at each predetermined evaluation time point (6, 12, 24, and 48 h and 7 days after surgery) will be compared between treatment groups. Additionally, the change in pain intensity from 6 h after the surgical procedure to 12, 24, and 48 h and day 7 after the procedure and the development of pain between 24 and 48 h will be compared between the intervention and control group. The number of patients in the group without primary tamponade who require tamponade dressings will also be documented.

Further secondary endpoints that will be compared between the treatment groups are the use of analgesics; the lowest hemoglobin documented in clinical routine within 7 days; quality of life using EuroQuol 5 dimensions (EQ. 5D) at screening, on discharge and on day 7 and patient satisfaction on day 7. Patient satisfaction will be measured using the key figures “subjective treatment errors”; “subjective treatment success”; the satisfaction index and the expectation fulfillment scale of the Cologne Patient Satisfaction Questionnaire of Pfaff et al. [26].

For safety analysis all expected and unexpected AEs and SAEs occurring in temporal relation to the clinical trial will be documented and compared between the treatment groups. Documentation includes the causal relationship with the therapy to be investigated and/or with the previous surgical treatment. The nature of the event and the onset, end, and severity (mild, moderate, severe) of each AE will be documented. A full overview of the visit plan and the schedule of enrollment, interventions, and assessments are provided in Figs. 2 and 3.

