## Methods/design

### Aim of the study

The primary aim of the study is to prove that in routine clinical practice, treating patients without a tamponade dressing after hemorrhoidectomy results in a lower pain burden, and is non-inferior to the use of tamponade in terms of the incidence of severe postoperative bleeding requiring surgical revision. 

Secondary aims are to assess all patients in the group without primary tamponade dressing after surgery who needed emergency tamponade, and to compare differences between the study groups in preoperative and postoperative hemoglobin values and the use of pain medications. Quality of life and patient satisfaction will also be compared between the two treatment groups.

The safety analysis aims to compare the number of adverse events (AE) and serious adverse events (SAE) in the two study groups in order to make a statement on the potential risk to patients without a tamponade dressing after hemorrhoidectomy.

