### Statistical analysis and power calculation

The analysis of the primary and secondary endpoints will be performed according to an adapted intention-to-treat (ITT) principle. There will be no interim analysis. The ITT analysis population will include all randomized participants who have undergone the surgical procedure (hemorrhoidectomy). The ITT analysis population will comprise participants assigned to the treatment group based on the randomization schedule, regardless of the treatment actually received. Randomization will be performed up to 12 h prior to the surgical intervention. However, without the surgical intervention there will be no postoperative wound that requires further treatment and thus there will be no data collected and analysis will not be possible. The study participant will therefore be excluded from the clinical trial if the scheduled surgery is not performed. Patients who are excluded from the trial after randomization and before the start of the observation period (postoperative wound care with or without tamponade) are replaced by another study participant in order to achieve the required number of cases. The randomization sequence will be continued. The next patient does not receive the randomized allocation of the excluded patient. The study will be continued until the required number of evaluable patients has been reached. Due to complications it may not be possible to comply with the randomly assigned treatment regimen in a very small number of patients. These patients will not be excluded from the study. Study participants will also be excluded from the clinical trial if a surgical procedure other than Milligan-Morgan or Parks is performed, which does not result in an open wound.

Details of participants’ baseline characteristics including preoperative pain and hemoglobin levels will be provided, but the data will not be compared statistically (by calculating the *p* value) because any differences between groups at this point must arise by chance (if randomized properly).

As a secondary approach, a per-protocol (PP) analysis will be performed excluding patients with any serious protocol deviations, if applicable. The safety analysis will be performed based on the as-treated (AS) population.

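### The pre-operative screening EQ-5D is listed among the endpoints compared between arms, against the protocol's own rule for baseline data; it should be described and used as a covariate

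*Protocol article*

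**What the plan says.** Four parts of the protocol article bear on this point.

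- **Aim of the study.** Quality of life is a secondary aim, stated without time points: "Quality of life and patient satisfaction will also be compared between the two treatment groups".
- **Primary and secondary outcomes.** The list opens with "Further secondary endpoints that will be compared between the treatment groups are" and includes "quality of life using EuroQuol 5 dimensions (EQ. 5D) at screening, on discharge and on day 7 and patient satisfaction on day 7". The three time points have the same status; nothing marks screening as the baseline.
- **Statistical analysis and power calculation, on baseline data.** The rule is "baseline characteristics including preoperative pain and hemoglobin levels will be provided, but the data will not be compared statistically". The reason given is that, under proper randomisation, a difference at that stage can only be chance.
- **The same section, on secondary endpoints.** It names tests for pain, lowest hemoglobin and adverse events, but none for the EQ-5D. It names factors that may influence pain, quality of life and satisfaction: mental illness, preoperative pain, concomitant pain therapy and type of tamponade. The screening EQ-5D is not among them. Detailed procedures are left to a statistical analysis plan.

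**The concern.** A value taken before the arms differ cannot be an outcome of the treatment. Listing it with the compared endpoints sets the outcomes section against the baseline rule, and an analyst who follows the list to the letter would do what the rule forbids.

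The listing also hides the useful role of this value. A pre-operative measurement on the same instrument is usually a good candidate predictor of the later scores, and it is planned for collection anyway. If it is treated as a third comparison and not as the baseline for the other two, precision in the discharge and day 7 comparisons is given up for nothing.

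**Working it through.** The protocol states no figure on this point, so there is none to reproduce. The check has two parts.

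**1. Is the screening EQ-5D baseline data under the protocol's own terms?**

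- The arms first differ at the end of surgery, when a tamponade is or is not placed after hemostasis (Intervention and comparison).
- The patient is not told the allocation before surgery (Design), so knowledge of it cannot colour a pre-operative answer.
- Consent precedes randomisation and every trial procedure (Participants). That screening also precedes randomisation is inferred from its name, because the visit figures are not shown. The conclusion does not need this: a pre-operative value from a patient unaware of the allocation cannot reflect the dressing.

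The screening EQ-5D therefore falls under the baseline rule. That rule gives preoperative pain and hemoglobin as examples, not as a closed list.

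The other outcomes are handled differently. The pain times to be compared are all postoperative, and change in pain is defined explicitly from 6 h. The hemoglobin endpoint is the lowest postoperative value up to day 7. Preoperative pain and hemoglobin are assigned to the baseline description. In the list of compared outcomes, only the EQ-5D has its pre-treatment value placed beside its post-treatment values.

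**2. What would using it as a covariate gain?**

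Let r be the correlation between the screening EQ-5D and the later EQ-5D. The documents give no value, so r = 0.3 to 0.6 is an assumption. With equal variances and a linear model, the variance of the treatment difference, relative to comparing the later values alone (= 1.00), is:

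- with screening as covariate: 1 − r²
- with change from screening: 2(1 − r)

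The equivalent gain in patients for the covariate analysis is 1/(1 − r²).

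| r (assumed) | Covariate, 1 − r² | Fall in variance | 1/(1 − r²) | Change score, 2(1 − r) |
|---|---|---|---|---|
| 0.3 | 1 − 0.09 = 0.91 | 9% | 1.10 | 1.40 |
| 0.4 | 1 − 0.16 = 0.84 | 16% | 1.19 | 1.20 |
| 0.5 | 1 − 0.25 = 0.75 | 25% | 1.33 | 1.00 |
| 0.6 | 1 − 0.36 = 0.64 | 36% | 1.56 | 0.80 |

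The covariate form is better than the later values alone and better than change scores throughout this range. Change scores are worse than the later values alone when r is below 0.5, so the way the baseline is used matters.

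**The case against.** The strongest reply is that the three time points are only a measurement schedule. The endpoint is quality of life, the aim is stated without time points, and no sentence says that each time point is tested separately. On this view the baseline rule already governs the screening value, and the rest belongs to the analysis plan. Much of this stands: the phrase may well have been meant as a schedule, and the absence of a stated adjustment model from an article is not in itself a fault. It does not remove the conflict in the wording, because the list is introduced as endpoints to be compared and screening is not set apart.

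Three stronger readings are tempting, and the documents do not support them.

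- **That the trial will test the screening EQ-5D, with a 1 in 20 chance of a false finding.** No test for the EQ-5D is stated at any time point, and the baseline rule argues against one at screening.
- **That a chance difference at screening would bias the later comparisons.** Under randomisation, an unadjusted comparison at discharge or day 7 is unbiased.
- **That the trial leaves the baseline unused.** The article does not exclude its use, and the analysis plan or the visit figures, neither of which is shown, may provide for it.

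**Conclusion.** The point holds as a conflict of wording with an easy improvement attached. Taken literally, the outcomes section puts a pre-operative value among the compared endpoints, while the statistical section says that such data are only described. No part of the article gives the screening EQ-5D a baseline role.

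The stake is precision on one secondary endpoint: a 9% to 36% lower variance of the treatment difference, equivalent to about 10% to 56% more patients for that endpoint. These figures rest wholly on the assumed correlation of 0.3 to 0.6 and measure the value of the covariate, not harm done by the wording. If the analysis plan already adjusts for the screening value, only the wording needs correcting. The primary outcomes and the sample size, which was calculated for bleeding needing revision, do not change.

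**What to change.** In the list of secondary endpoints, name the EQ-5D at discharge and the EQ-5D at day 7 as the values compared between arms, and take screening out of that list. Add that the screening EQ-5D is reported descriptively by arm with the other baseline characteristics, without a test. State, in the protocol or the analysis plan, that each of the two comparisons uses a model with treatment arm and the screening EQ-5D as covariate.

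The cost is a sentence or two, settled before the data are analysed. No further data collection is needed, because the questionnaire is already scheduled at screening.

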**Fig. 2 Fig2:**
[figure not shown]
Visit plan. Schematic overview of study visits and postsurgical pain assessment time points

**Fig. 3 Fig3:**
[figure not shown]
Schedule of enrolment, interventions and assessments according to SPIRIT

### Statistical analysis and power calculation

The analysis of the primary and secondary endpoints will be performed according to an adapted intention-to-treat (ITT) principle. There will be no interim analysis. The ITT analysis population will include all randomized participants who have undergone the surgical procedure (hemorrhoidectomy). The ITT analysis population will comprise participants assigned to the treatment group based on the randomization schedule, regardless of the treatment actually received. Randomization will be performed up to 12 h prior to the surgical intervention. However, without the surgical intervention there will be no postoperative wound that requires further treatment and thus there will be no data collected and analysis will not be possible. The study participant will therefore be excluded from the clinical trial if the scheduled surgery is not performed. Patients who are excluded from the trial after randomization and before the start of the observation period (postoperative wound care with or without tamponade) are replaced by another study participant in order to achieve the required number of cases. The randomization sequence will be continued. The next patient does not receive the randomized allocation of the excluded patient. The study will be continued until the required number of evaluable patients has been reached. Due to complications it may not be possible to comply with the randomly assigned treatment regimen in a very small number of patients. These patients will not be excluded from the study. Study participants will also be excluded from the clinical trial if a surgical procedure other than Milligan-Morgan or Parks is performed, which does not result in an open wound.

Details of participants’ baseline characteristics including preoperative pain and hemoglobin levels will be provided, but the data will not be compared statistically (by calculating the *p* value) because any differences between groups at this point must arise by chance (if randomized properly).

As a secondary approach, a per-protocol (PP) analysis will be performed excluding patients with any serious protocol deviations, if applicable. The safety analysis will be performed based on the as-treated (AS) population.

In order to address the primary aim of the study to prove that treating patients without a tamponade dressing after hemorrhoidectomy results in a lower pain burden while the incidence of bleeding requiring surgical revision is no greater than in the patients treated with tamponade (non-inferiority), the primary outcome variables will be examined in terms of an a priori ordered hypothesis at a level of significance of 0.05. Pain values will be described by the mean (SD) and median (IQR). The last observation carried forward (LOCF) method will be used to replace missing values for pain, but only if at least one documentation of postoperative pain is available. Differences in pain will be analyzed using the non-parametric U test (two-sided; alpha = 0.05). If significantly lower pain levels are detected in the treatment arm without tamponade, non-inferiority in the bleeding rate will be also be analyzed at the 5% significance level. Alpha error correction is not required [27]. The incidence of postoperative bleeding needing revision (bleeding rate) will be determined in both treatment arms and will be tested for non-inferiority by calculating the 90% confidence interval (CI) (one-sided hypothesis), with a rate of bleeding two times higher considered acceptable, whereas a bleeding rate three times higher will no longer be considered non-inferior. This rate difference (together with the 90% CI margins) will be considered in relation to the observed revision rate in the control arm. This gives the estimator for the relative increase together with the confidence margins. If the upper limit of this relative increase exceeds 3, then a threefold increase is still possible and non-inferiority is rejected. If the upper limit of this relative increase is < 3, non-inferiority is assumed (with an error rate of 5%). In the unexpected case that the revision rate in the control group is rather low (< 2%) or even 0%, the relative increase will not be calculated. In this case, only the revision rates in the treatment groups are reported (with the 95% CI). The number of patients requiring tamponade in the postoperative course in the group that did not receive primary tamponade after surgery will be presented with the 95% CI.

Pain values at all predetermined survey times and the development of pain between selected time points will be compared in the two treatment groups using the U test. The lowest hemoglobin values in the postoperative period up to day 7 will be compared in the two treatment groups using the two-sided *t* test. The amount and type of postoperative pain medication will be described by percent values for each treatment group. For the safety analysis the incidence of AEs and SAEs by category (severity) will be compared in the two treatment groups using Fisher’s exact test.

There will be no a priori planned subgroup analysis, but a multivariate analysis of all study patients (ITT population) will be performed investigating the occurrence of severe postoperative bleeding (dependent variable). In this logistic regression, the following variables are considered as possible predictors (independent variables): age, gender, surgical method used (Milligan-Morgan or Parks), severity of hemorrhoids (grade III/IV), use of tamponade (yes/no), type of tamponade used, type of anesthesia used, occurrence of intraoperative complications, preoperative hemoglobin levels, type and amount of pain therapy (in particular the performance of a pudendal block), and type and amount of anticoagulation therapy. If this multivariate analysis shows that there is a significant predictor of bleeding that is not evenly distributed within the two study groups (significance in demonstrating the comparability of the two groups), a subgroup analysis of this variable will be performed. In this case, primary and secondary endpoints will be analyzed as described previously, in the subgroups of the unequally distributed variable.

Mental illness in the study participants, preoperative pain levels, the use and type of concomitant pain therapy, and the type of tamponade used represent factors possibly influencing pain, quality of life, and patient satisfaction. The influence of these factors on the aforementioned outcomes will be examined.

Based on the results of the single-center pilot study that demonstrated significant pain reduction (first primary outcome) without tamponade, it can be assumed with great probability that an advantage can also be demonstrated in this much larger multicenter study (first hypothesis). For the second primary outcome based on the results of the pilot study and the international literature it is predicted that 4% of the patients will need surgical revision with tamponade due to severe postoperative bleeding in the treatment group (96% estimated success rate in the control group).

In the intervention group without tamponade a slightly higher rate of bleeding needing surgical revision of ca. 8% is expected. The bleeding rate was 10% in 52 cases included in the pilot study. Therefore, the clinically acceptable and justified limit for non-inferiority is set at 12%, or 8% higher than in the control group with tamponade (8% non-inferiority limit).

Based on these assumptions, the sample size is 433 per group, or 866 patients in total. For study enrollment, assuming a maximum 10% rate of loss to follow up, 953 patients are required. The power was set at 80% in all calculations. Detailed procedures for executing the statistical analysis of the primary and secondary variables and other data will be provided in a statistical analysis plan.

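### Read literally, the bleeding rule tests the relative increase against 3, a fourfold rate, while the plan's own limit is threefold (12% vs 4%, 8 points)

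*Protocol article*

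**What the plan says.** Everything on this point is in the protocol article under Statistical analysis and power calculation, in two places.

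**Decision rule.** Non-inferiority is judged with a 90% interval, one-sided at 5%. The limit is first put in words: "a rate of bleeding two times higher considered acceptable, whereas a bleeding rate three times higher will no longer be considered non-inferior". The quantity to be tested is then built up: "This rate difference (together with the 90% CI margins) will be considered in relation to the observed revision rate in the control arm". The article names the result the relative increase and gives the cut-off: "If the upper limit of this relative increase exceeds 3, then a threefold increase is still possible and non-inferiority is rejected". An upper limit under 3 leads to non-inferiority, with a stated error of 5%. If the control rate is under 2%, the relative increase is not calculated.

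**Sample size.** For the control arm, "it is predicted that 4% of the patients will need surgical revision with tamponade due to severe postoperative bleeding"; without tamponade, "a slightly higher rate of bleeding needing surgical revision of ca. 8% is expected". The margin follows: "the clinically acceptable and justified limit for non-inferiority is set at 12%, or 8% higher than in the control group with tamponade". With 80% power this gives 433 per group.

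**The concern.** A difference divided by the control rate is not a rate ratio; it is the rate ratio minus 1. The cut-off of 3 fits the ratio, but the article attaches it to the difference divided by the control rate. There the threefold limit is 2, and 3 stands for fourfold. The section therefore holds two different limits for the second primary hypothesis: one that was justified and used to size the trial, and a looser one in the sentence that decides the result.

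An analyst who follows the definition could report that omitting tamponade is non-inferior for bleeding that needs surgical revision after observing a tripled rate. The article itself says that such a rate does not qualify.

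**Working it through.** **Inputs** (all from the section named above): control rate pC = 4%; expected rate without tamponade pT = 8%; limit 12%, or 8 points; one-sided 5% (z = 1.645); power 80% (z = 0.8416); 433 per group.

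**1. Reproduce the sample size.** n = (1.645 + 0.8416)² × [pC(1−pC) + pT(1−pT)] / (margin − (pT − pC))².
- The variance term is 0.04×0.96 + 0.08×0.92 = 0.112.
- 8-point margin: 6.183 × 0.112 / 0.04² = 432.8, so 433, as stated.
- 12-point margin: 6.183 × 0.112 / 0.08² = 108.2, so 109.

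The trial was sized on 8 points.

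**2. Put the limits on the written scale, (pT − pC)/pC.**
- 12% vs 4%: (12 − 4)/4 = 2, rate ratio 3.
- 16% vs 4%: (16 − 4)/4 = 3, rate ratio 4.

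Because the divisor is the observed control rate, the margin implied by 3 is not constant. It is 3 × 2% = 6 points at 2%, 12 points at 4%, and 18 points at 6%.

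**3. Examples with 17/433 (3.93%) in the control arm, Wald 90% interval.**
- 51/433 (11.78%), observed ratio 3.0: the difference is 7.85 points and its upper limit 10.83 points. 10.83/3.93 = 2.76, below 3, so the written rule passes it.
- 54/433 (12.5%), observed ratio 3.18: 11.57/3.93 = 2.95, passes.
- 55/433: 11.82/3.93 = 3.01, fails.

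Both passing results fail an 8-point limit. They also fail a ratio limit of 3, since the estimate itself is already at or above 3.

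**4. Probability of declaring non-inferiority.** Exact binomial enumeration, 433 per arm, true control rate 4%. For the two relative-increase rules and the ratio rule, no test is made if the observed control rate is below 2%; this happens in 0.9% of trials.

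| Rule | True 8% | True 12% | True 16% |
|---|---|---|---|
| Relative increase < 3 (as written) | 91.7% | 59.0% | 21.2% |
| Relative increase < 2 | 66.4% | 17.5% | 1.7% |
| Difference < 8 points | 79.5% | 5.6% | 0.02% |
| Rate ratio < 3 (log interval) | 40.9% | 5.4% | 0.2% |

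**5. Separate the two sources of the 59%.** The rule with cut-off k passes when pT − (1+k)pC, in observed rates, lies below −1.645 × SE, where SE is that of the simple difference. At 12% vs 4%, SE = √[(0.0384 + 0.1056)/433] = 0.0182, and 1.645 × SE = 0.0300. The true spread is larger, because the control rate enters with weight 1+k.
- k = 2: mean 0, SD = √[(0.1056 + 9×0.0384)/433] = 0.0323. Φ(−0.0300/0.0323) = about 17.6%.
- k = 3: mean 0.12 − 0.16 = −0.04, SD = √[(0.1056 + 16×0.0384)/433] = 0.0408. Φ((0.04 − 0.0300)/0.0408) = about 59.7%.

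Both agree with the enumeration. Moving the cut-off from 3 to 2 removes 59.0 − 17.5 = 41.5 percentage points. The remaining excess over 5% comes from dividing by an observed rate as though it were known.

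**6. Check the ratio alternative.** At 8% vs 4% the SE of the log ratio is √[0.96/(433×0.04) + 0.92/(433×0.08)] = 0.286. Power = Φ(ln(3/2)/0.286 − 1.645), about 41%.

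**The case against.** The best defence is that a rate ratio was meant. The article prints no formula, and *considered in relation to* is loose wording. The limit is put in ratio terms three times: twofold acceptable, threefold not, and an upper limit above 3 glossed as a possible threefold increase. The 12% limit agrees with that. Details are also deferred to an analysis plan that is not shown.

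Much of this stands as a guide to intent. A reader might infer that the trial set out to accept a fourfold bleeding rate; the documents do not support that, and the sample size speaks against it. But the rule does name a rate difference, relate it to the control rate and call the result a relative increase. Two careful analysts could reach opposite conclusions on 51 vs 17 events. A primary rule that is stated inconsistently is not cured by deferring detail.

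Two further objections are right and limit the point. The 12-point margin holds only at an observed control rate of 4%; below 8/3 = 2.67% the written rule is even tighter than 8 points. And the 59% may not be charged to the cut-off alone, as step 5 shows.

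**Conclusion.** The concern holds as an internal contradiction in the decision rule of a primary endpoint, and it must be resolved before analysis. Read literally, the rule tests against a fourfold rate, whereas the same section declares threefold unacceptable and sizes the trial on 12% vs 4%.

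At the plan's own limit, false non-inferiority is about 59% instead of 5%. Of this, 17.5% would remain with a cut-off of 2. These figures assume 433 evaluable patients per arm, a true control rate of 4% and a Wald interval for the difference, since the article does not name the interval method.

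A reader might also infer that replacing 3 by 2, or reading the rule as a rate ratio, restores the planned properties. Neither does: the first leaves the error at 17.5%, and the second roughly halves the power. Nor does the finding make the 433 wrong; that figure is correct for the 8-point margin.

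**What to change.** Replace the rule by: *non-inferiority is concluded if the upper limit of the 90% CI for the rate difference (without minus with tamponade) is below 8 percentage points*. Show the relative increase descriptively, with no decision threshold. This matches the stated margin and the sample size: exact power 79.5% at 8% vs 4%, error 5.6% at 12% vs 4%.

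The cost is one sentence in the protocol and the analysis plan, with no change in patient numbers. Success becomes harder than under the literal rule (79.5% against 91.7% at the expected rates), but as hard as was planned. Two consequences should be stated:
- The exception for control rates under 2% was tied to calculating the relative increase. Say whether it stays; the 79.5% and 5.6% were computed without it.
- Eight points equals threefold only at a 4% control rate. At 2% it would allow 10%, which is fivefold.

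If a rate-ratio limit of 3 is preferred for that reason, use a proper confidence interval for the ratio and restate the power, which is about 41% at 433 per group, or recalculate the sample size.
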